### Recruitment

2.6

All patients diagnosed with HD II-III stage will be considered for this study.

### Assignment of interventions

2.7

#### Allocation

2.7.1

Participants will be randomly assigned to either control or experimental group with a 1:1 allocation ratio using fixed block randomization with a computerized random number generator. All subjects will be allocated preoperatively.

#### Blinding

2.7.2

All relevant data from patient chart except patients’ names and the stapler used during surgery will be transferred into an electronic case report form (eCRF). The eCRF should contain results of all the screening procedures, including patient history and demographics, imaging studies, filled-out questionnaires, operation note, and postoperative rounds during patients’ stay in the surgical ward.

### Data collection, management, and analysis

2.8

#### Data collection methods

2.8.1

All data will be collected prospectively using eCRFs designed for this trial. The reasons for withdrawal will be documented. The investigator will attempt to contact each participant at least 3 times during each follow-up window before declaring them lost for observation. The study exit form will be recorded in the eCRF. All prior data will be analyzed within the research.

#### Data management

2.8.2

All patients will receive clarifications of all the study procedures, and will be able to discuss them with the primary investigator. All patient data will be handled according to the principles of doctor–patient confidentiality; the subjects will be anonymized and analyzed with individual identifier numbers transcribed into eCRF.

#### Statistical methods

2.8.3

An intention-to-treat analysis will be performed. Statistical analysis was carried out using IBM SPSS Statistics v23 software (IBM Corporation, US, New York), and included a comparison of categorical (Fisher exact test) and quantitative (unpaired Student *t* test) indicators in groups. The results were considered statistically significant, with a value of *P* ≤ .05.

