### Trial design

1.3

HAND study is a prospective, randomized, controlled, unicenter, noninferiority, parallel group, 2-arm trial with 1:1 allocation ratio. Randomization will be performed using block method before the procedure.

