### Sample size

2.5

Considering that this is a noninferiority study, the sample size was calculated using 1-sided Blackwelder test.^[5]^ According to published data, the incidence of recurrence rate of suture ligation of the hemorrhoidal arteries with mucopexy varies from 20% to 30%.^1^,^2^,^3^,^4^ The expected incidence of recurrence rate of HD after digital detection of hemorrhoidal arteries pulsation followed by suture ligation and mucopexy is not more than 35%. The purpose of this study is to show that the outcomes of HAL-RAR procedure with digital detection of hemorrhoidal arteries is noninferior compared to HAL-RAR procedure with Doppler-guided hemorrhoidal arteries detection.

Considering that a = 0.05; the statistical power of the study is 80%; the patients are randomized into 2 groups with 1:1 allocation ratio; the noninferiority margin D = 5%, the required sample size is 204 patients (102 patients in each of the 2 groups).

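### Intention-to-treat is the only analysis set named for a noninferiority comparison, and it is mildly anti-conservative if some patients do not receive the assigned detection method

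*Protocol article*

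**What the plan says.** Trial design (1.3) describes a "noninferiority, parallel group, 2-arm trial with 1:1 allocation ratio". Sample size (2.5) sets the margin at 5 percentage points with 102 patients per arm, and says that "the sample size was calculated using 1-sided Blackwelder test", with alpha 0.05 and 80% power.

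On the analysis set, Statistical methods (2.8.3) has one sentence: "An intention-to-treat analysis will be performed". The article names no per-protocol or as-treated set.

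On patients who leave, Data collection methods (2.8.1) says: "The investigator will attempt to contact each participant at least 3 times during each follow-up window before declaring them lost for observation". It adds that withdrawal reasons are documented, that an exit form is recorded, and: "All prior data will be analyzed within the research". It does not say how a patient with incomplete follow-up is classified for recurrence.

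Allocation (2.7.1) is preoperative. Under Blinding (2.7.2), the operation note is among the contents of the eCRF.

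**The concern.** In a superiority trial, intention-to-treat is the cautious choice, because departures from the assigned treatment make the arms look more alike and so work against the claim. In a noninferiority trial the same dilution works in favour of the claim. A second analysis, restricted to patients who received the assigned technique, is the usual check.

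Departures are conceivable here. Allocation precedes surgery, while the finger-guided technique depends on what the surgeon can feel during the operation. If some patients are treated with the other detection method, a finger-guided technique that is worse by the full margin would pass somewhat more often than the nominal 5%. The article states no supporting analysis that would show whether the conclusion depends on such patients.

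**Working it through.** **Inputs from the article.** Margin 5 points, 102 per arm, one-sided alpha 0.05, power 80% (Sample size, 2.5). For rates, the section says that "the incidence of recurrence rate of suture ligation of the hemorrhoidal arteries with mucopexy varies from 20% to 30"%, and that the expected rate after "digital detection of hemorrhoidal arteries pulsation followed by suture ligation and mucopexy is not more than 35"%. The article gives no crossover or dropout rate, so 5%, 10% and 20% are assumed.

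**The plan's own figure.** The unpooled Blackwelder formula is

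n per arm = [pc(1−pc) + pt(1−pt)] × (z0.95 + z0.80)² / (margin − (pt − pc))²

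where pc is the Doppler-guided rate and pt the finger-guided rate. With pc = 0.30 and pt = 0.20, this is (0.21 + 0.16) × 6.183 / 0.15² = 101.7, so 102 per arm and 204 in total. The stated size is reproduced, but only with the finger-guided technique assumed 10 points better, not with the stated 35%. That is a separate matter. It is noted here because the 102 per arm is used below.

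**Effect of crossover under intention-to-treat.** Take the boundary case pc = 0.30, pt = 0.35, a true excess equal to the margin. Assume a fraction x of patients receive the other technique and take on its recurrence risk.

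- Finger-guided arm only: the rate there becomes 0.35 − 0.05x, and the difference 0.05(1 − x).
- Both arms: the rates become 0.30 + 0.05x and 0.35 − 0.05x, and the difference 0.05(1 − 2x).

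By normal approximation, with SE = √{[pc(1−pc) + pt(1−pt)]/102} at the diluted rates, the chance of declaring noninferiority is Φ[(0.05 − difference)/SE − 1.645].

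| x | Difference, finger arm only | False claim | Difference, both arms | False claim |
|---|---|---|---|---|
| 0 | 5.00 points | 5.0% | 5.0 points | 5.0% |
| 5% | 4.75 | 5.4% | 4.5 | 5.8% |
| 10% | 4.50 | 5.8% | 4.0 | 6.8% |
| 20% | 4.00 | 6.8% | 3.0 | 9.0% |

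For example, at x = 20% in the finger-guided arm: SE = √[(0.21 + 0.2244)/102] = 0.0653, 0.01/0.0653 = 0.153, and Φ(0.153 − 1.645) = 6.8%.

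**Effect of dropout.** The result depends on a classification rule that the article does not give.

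- Equal loss of 5%, 10% or 20% in both arms, all lost patients counted as recurrence-free: the difference becomes 4.75, 4.5 or 4.0 points and the false-claim rate 5.4%, 5.9% or 6.9%.
- The same loss, but with all recurrences among lost patients already recorded: 5.0%.
- Complete cases, with loss unrelated to outcome: 5.0%.
- Unequal loss counted as recurrence-free, true rates 30% in both arms: with 10% lost under Doppler and 5% under finger guidance, the difference is 0.30 × 0.95 − 0.30 × 0.90 = +1.5 points, against noninferiority. Reversing the losses gives −1.5 points, towards it.

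The direction of any dropout bias is therefore not fixed.

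**The case against.** The strongest reply is that the article does not say intention-to-treat is the only analysis. A per-protocol set and missing-data rules may stand in a full protocol or analysis plan that is not shown. This stands in part: the point is limited to the set that the article names, which for a noninferiority question is not by itself the cautious one.

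A second reply is that crossover is speculative. The treatment is a single operation, the Interventions section describes two separate techniques with no conversion between them, and no rate is given. This also stands, and is why the figures are conditional and the effect is called mild.

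Three stronger readings are tempting, and the article does not support them.

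- A reader might infer that patients lost without symptoms count as recurrence-free, so that dropout also favours noninferiority. Data collection methods says only that earlier data are analysed. Even under the inferred rule, unequal loss can move the difference either way.
- A reader might infer that a true 6-point excess diluted by 20% crossover to 0.06 × 0.8 = 4.8 points would meet the margin. The decision rests on the upper confidence limit, not on the point estimate. At rates of 30% and 34.8% the SE is about 6.5 points, and the one-sided 95% upper limit is 4.8 + 1.645 × 6.545 = 15.6 points, far outside the margin. The chance of declaring noninferiority rises only from about 3.6% to 5.3%.
- A reader might infer that departures would go unseen. The operation note, withdrawal reasons and exit form are all recorded, so the data for the check exist.

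Finally, section 2.8.3 plans Fisher exact and t tests and no comparison with the margin at all. That is a larger defect, but correcting it does not settle this one: a margin comparison still needs its analysis sets stated.

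**Conclusion.** The point holds in a limited form. Intention-to-treat is the only set named for a noninferiority comparison with a 5-point margin, and it is mildly anti-conservative if patients do not receive the assigned detection method. Under assumed crossover of 5% to 20%, the false-claim rate at a true 5-point excess rises from 5.0% to about 5.4% to 6.8% (finger-guided arm) or 5.8% to 9.0% (both arms).

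These figures rest on rates of 30% and 35%, 102 per arm, a one-sided 0.05 test against the margin, the normal approximation, and the assumption that crossed-over patients take on the risk of the technique received. Without crossover there is no inflation from this source. On dropout, the supported conclusion is only that the handling of patients without a final status is unstated and that the direction of any bias is open.

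**What to change.** In section 2.8.3:

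1. Add a per-protocol analysis of recurrence alongside intention-to-treat, restricted to patients who received the assigned detection method as shown by the operation note in the eCRF.
2. Compare both analyses with the 5-point margin, and require consistent conclusions before claiming noninferiority.
3. State how patients without a final recurrence status enter the endpoint, and add a sensitivity analysis for them, for instance a tipping-point analysis that assigns progressively worse outcomes to those missing in the finger-guided arm.

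The cost is a little extra analysis on data already planned for collection, and a noninferiority claim that becomes slightly harder to make.

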##### Primary objective

1.2.2.1

To determine if the palpation-guided hemorrhoidal arteries ligation and mucopexy is noninferior to Doppler-guided ligation of hemorrhoidal arteries and mucopexy in patients with II-III grade HD at the endpoint of recurrence rate determined by physical examination and patients complaints.

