#### Primary outcome measure

2.4.1

The recurrence of HD is determined as presence any of initial symptoms or appearance of any new symptom of HD: anal bleeding during defecation, prolapse of hemorrhoidal piles, chronic pain, or their combinations.

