## Discussion

3

The results of this RCT may demonstrate the absence of significant advantages in Doppler guidance technology for hemorrhoidal arteries detection in HAL-RAR procedures compared with the simple and accessible to any surgeon finger-guided hemorrhoidal arteries detection concerning the efficiency in eliminating hemorrhoidal prolapse and/or hemorrhoidal bleeding. We will analyze frequency of postoperative complications, the intensity of the pain syndrome, the relapse rate, and individual QOL level. It will allow us to conclude whether the HAL-RAR with finger hemorrhoidal artery detection is effective and safety procedure for hemorrhoids disease treatment.

The design of this study has certain limitations. Firstly, there is quite often mismatching of doctors regarding the stage of the HD as well as stage of each hemorrhoidal pile. So the group might be heterogenic regarding the preoperative stage of the HD.

Another issue is the uncertainty of the definition of HD recurrence after surgery. In this protocol, we determined it as appearance of any new symptoms of HD or persistence of previous ones. But we suppose that nevertheless procedure might be effective for preoperatively existed symptoms new ones might appear. So we will try to figure out the difference of preexisting symptoms resolution and appearance of new ones.

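### A noninferiority trial with a 5-point margin is analysed with a Fisher exact test of no difference, which never uses the margin

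*Protocol article*

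**What the plan says.** All references are to the protocol article.

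- **Primary objective (1.2.2.1):** to find out whether the palpation-guided procedure "is noninferior to Doppler-guided ligation of hemorrhoidal arteries and mucopexy", judged on recurrence. Trial design (1.3) also calls the study a noninferiority trial.
- **Primary outcome measure (2.4.1):** "The recurrence of HD is determined as presence any of initial symptoms or appearance of any new symptom of HD". This is a yes/no outcome.
- **Sample size (2.5):** "the sample size was calculated using 1-sided Blackwelder test", with alpha 0.05, 80% power, a margin of 5% and 102 patients per arm. Published recurrence is put at 20% to 30%, and recurrence in the finger-guided arm at no more than 35%.
- **Statistical methods (2.8.3):** "An intention-to-treat analysis will be performed". The analysis "included a comparison of categorical (Fisher exact test" and a Student t test for quantitative variables. The decision threshold is: "The results were considered statistically significant, with a value of *P* ≤ .05". The section gives no margin, no confidence limit for the difference and no noninferiority test.
- **Discussion (3):** the results "may demonstrate the absence of significant advantages in Doppler guidance technology".

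**The concern.** The objective and the sample size pose one question: is the excess recurrence with finger guidance below 5 points? The analysis section answers another: is there evidence of any difference at all? Fisher's null hypothesis is equal recurrence. Failing to reject it says nothing about whether an excess of 5 points or more has been ruled out. The one Fisher result that would bear on the objective is a significant advantage for finger guidance, and the trial does not set out to show that.

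The Discussion describes the hoped-for result as a lack of significant advantage for Doppler, which invites a non-significant P value to be read as the positive finding. Under that reading the incentives reverse: the smaller the trial or the noisier the outcome, the more likely it is to appear to succeed, and the 5% error rate used in planning no longer applies to the claim.

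**Working it through.** **Inputs (Sample size, 2.5, and Statistical methods, 2.8.3).** n = 102 per arm; margin 5 points; one-sided alpha 0.05; control recurrence 20% to 30%; finger-guided recurrence up to 35%; Fisher exact test with P ≤ .05. Two assumptions are mine. Fisher is two-sided, because 2.8.3 does not give the sidedness (the one-sided case is in step 5). All 102 patients per arm are analysed.

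**1. The plan's own figure.** The Blackwelder formula per arm is n = [pC(1−pC) + pT(1−pT)] × (z₀.₉₅ + z₀.₈₀)² / [margin − (pT − pC)]², with (1.645 + 0.842)² ≈ 6.18.

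- With pC = 30% and pT = 35%, the denominator is (0.05 − 0.05)² = 0, so no finite n exists. With pC below 30% and pT = 35%, the excess is beyond the margin.
- With equal rates of 25%: 0.375 × 6.18 / 0.0025 ≈ 928 per arm.
- With the stated alpha, power and margin, among rates of 20% to 35% in 5-point steps, 102 per arm appears only for pC = 30% and pT = 20%: 0.37 × 6.18 / 0.0225 ≈ 102. That is the reverse of the stated expectation.

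So 204 does not reproduce from the stated rates. This is a separate fault, but it bears on the fix.

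**2. What a non-significant Fisher result can hide.** The first row is worked in step 3. The other three are the largest finger-arm excesses that stay non-significant for 20, 26 and 31 control recurrences (control rates of about 20%, 25% and 30%).

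| Doppler /102 | Finger /102 | Excess (points) | Fisher P | One-sided 95% upper limit (points) |
|---|---|---|---|---|
| 25 | 38 | 12.7 | 0.069 | 23.3 |
| 20 | 33 | 12.7 | 0.055 | 22.7 |
| 26 | 40 | 13.7 | 0.051 | 24.4 |
| 31 | 45 | 13.7 | 0.059 | 24.7 |

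In each of the last three rows, one more finger-arm recurrence makes the result significant (P = 0.039, 0.036 and 0.043).

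**3. The limit for the first row.** Rates are 25/102 = 0.245 and 38/102 = 0.373, so the difference is 13/102 = 0.127. The standard error is √[(0.245 × 0.755 + 0.373 × 0.627)/102] = 0.064. The upper limit is 0.127 + 1.645 × 0.064 = 0.233, or 23.3 points against a margin of 5. These are Wald limits.

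**4. How often each rule passes.** Binomial probabilities were summed over all 103 × 103 possible outcomes. The margin-based rule is: one-sided 95% upper Wald limit below 5 points.

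| True Doppler vs finger | Excess (points) | Fisher non-significant | Margin-based rule passes |
|---|---|---|---|
| 20% vs 20% | 0 | 96.7% | 22.8% |
| 25% vs 25% | 0 | 96.6% | 20.8% |
| 30% vs 30% | 0 | 96.4% | 19.8% |
| 20% vs 25% | 5 | 89.6% | 5.1% |
| 25% vs 30% | 5 | 90.3% | 5.1% |
| 30% vs 35% | 5 | 90.9% | 5.1% |
| 20% vs 30% | 10 | 67.9% | 0.7% |
| 25% vs 35% | 10 | 70.6% | 0.8% |
| 20% vs 35% | 15 | 37.9% | 0.1% |

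At the margin with 30% versus 35%, 90.9/5 ≈ 18: reading non-significance as success would carry about 18 times the planned error.

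**5. One-sided Fisher instead.** The largest non-significant excess falls to 10.8 points (20 vs 31, P = 0.053; 25 vs 36, P = 0.063) or 11.8 points (31 vs 43, P = 0.054). Non-significance becomes 85% at 30% versus 35%, and 59% at 25% versus 35%.

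**The case against.** - **No rule says that non-significance is success.** This is correct. Statistical methods defines only what counts as significant, and the Discussion is loose narrative that names no criterion. The 13-point and 91% figures are therefore conditional on that reading. The mismatch itself is not conditional: whatever rule is applied, the stated test does not use the margin.
- **The section never names the primary outcome, and a noninferiority test is cited elsewhere.** Both are true. However, recurrence is binary and so falls under the categorical outcomes, with no exception made and no other analysis offered. The Blackwelder test is invoked only for the sample size.
- **An unseen analysis plan may hold the right test.** A missing interval method or decision rule alone would be no finding in a condensed article. Here the article states a method, and that method conflicts with its own objective. A plan that did otherwise would contradict the published text.
- **Sidedness is assumed.** This stands, so the range is shown: about 11 to 14 points across the two readings. The conclusion does not change.
- **The fix is not free, because the correct test has little power at 102 per arm.** The power figure is right (20% to 23% at equal rates of 20% to 30%). It comes from the sample size calculation rather than from choosing the correct test, but the two have to be dealt with together.

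**Conclusion.** The concern holds, and the plan is wrong as written. The one analysis stated for binary outcomes cannot answer the primary objective. With 102 analysed per arm and control recurrence of 20% to 30%, a two-sided Fisher test leaves an excess of 12.7 to 13.7 points non-significant, more than 2.5 times the margin; a one-sided test leaves 10.8 to 11.8 points. If non-significance is taken as success, a procedure truly at the margin would pass about 90% of the time instead of about 5%, and one truly 10 points worse would pass 68% to 71% of the time instead of under 1% (two-sided). Those percentages rest on that reading, which the Discussion invites but does not fix as a rule. The finding that the test ignores the margin rests on no assumption.

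**What to change.** Rewrite the primary analysis in Statistical methods (2.8.3):

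1. Estimate the risk difference in recurrence, finger minus Doppler, with a one-sided 95% upper confidence limit by a score method (Miettinen–Nurminen or Farrington–Manning).
2. Conclude noninferiority only if that limit is below +5 points.
3. Keep Fisher's exact test for the secondary categorical comparisons, and state its sidedness.
4. Say in the Discussion that a non-significant difference will not be read as noninferiority.

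The change costs one paragraph and a standard routine, with no new data. It should be made together with a review of the sample size. Under the correct rule, 102 per arm would require the finger arm to do about 4 to 6 points better in the observed data (at most 16 vs 20, 21 vs 26 or 25 vs 31 recurrences). At equal true rates of 20% to 30%, 80% power needs 792 to 1,039 patients per arm.

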#### Secondary outcome measures

2.4.2

1.The pain score after surgery will be measured by patient-reported pain level using visual scale ranging from 1 to 10 where 1 is “no pain" and 10 is the worst pain imaginable in 1 and 2 months after surgery.2.QOL assessment (patients satisfaction level): Patients will be asked to rate their own satisfaction of the procedure on a scale from 1 to 10 (with 10 being the best) and were asked whether the procedure helped their symptoms in 6 month and 1 year after surgery.3.Early postoperative complications rate (time frame: 30 days): The rate of complications in 30 days after surgery.

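### Optional improvement: for the yes/no secondary outcomes, an exact unconditional test such as Boschloo's would gain a few points of power over Fisher's test within the same 5% limit

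*Protocol article*

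**What the plan says.** Section 2.8.3 (Statistical methods) assigns one test to every categorical indicator: the analysis "included a comparison of categorical (Fisher exact test"). It then sets the threshold: "The results were considered statistically significant, with a value of *P* ≤ .05". It does not say whether that P value is one- or two-sided.

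Two items in section 2.4.2 (Secondary outcome measures) are, or could be, binary:
- early complications, defined as "The rate of complications in 30 days after surgery";
- a question attached to the satisfaction score, under which patients "were asked whether the procedure helped their symptoms in 6 month and 1 year after surgery". Its response options are not given.

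Pain and satisfaction are 10-point scales, so Fisher's test does not concern them. No expected rate is given for complications or for the symptom question.

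The only power statement is in section 2.5 (Sample size): "a = 0.05; the statistical power of the study is 80" percent, for 102 patients per arm. It belongs to the noninferiority calculation on recurrence, since "the sample size was calculated using 1-sided Blackwelder test".

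**The concern.** Fisher's test computes its P value conditionally on the total number of events in both arms. In a two-arm trial that total is random. For any given total, only a few P values are possible, and the largest one not exceeding .05 is often well below it. Averaged over the totals that can occur, the true type I error falls short of 5%, most of all when events are few.

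What is at stake is power for the secondary comparisons. The number of patients is set by the recurrence calculation, so these comparisons must make do with 102 per arm. Complications may well be infrequent, which is where the shortfall is largest: a real difference would then be reported as not significant more often than the 5% limit requires.

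**Working it through.** **Inputs.** 102 per arm and 1:1 allocation (section 2.5); Fisher's exact test at P ≤ .05 (section 2.8.3). Assumed: two-sided P, no dropout, and the event rates shown.

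**Where 102 comes from.** The usual unpooled noninferiority formula is n = (z₀.₉₅ + z₀.₈₀)² × [pC(1−pC) + pT(1−pT)] / (margin + pC − pT)². With 30% recurrence under Doppler guidance and 20% under palpation it gives 6.183 × (0.21 + 0.16) / 0.15² = 101.7, hence 102. Section 2.5 does not state that pair of rates, and it is a separate matter. Here it matters only that 102 does not depend on Fisher's test. The plan states no size or power for Fisher's test that could be reproduced.

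**Method.** With x and y events in the two arms, each from 0 to 102, there are 103 × 103 possible tables. For a rejection region R,

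Pr(reject | p₁, p₂) = Σ over (x, y) in R of Bin(x; 102, p₁) × Bin(y; 102, p₂).

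Setting p₁ = p₂ gives the true size; p₁ ≠ p₂ gives power. Fisher's region is all tables with two-sided Fisher P ≤ .05. Boschloo's region is all tables with Fisher P ≤ c, where c is the largest cutoff whose size, maximised over the common rate, stays at or below 5%. Here c = 0.065.

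**One table as illustration.** For 0 v 5 events, Fisher P = 2 × (102·101·100·99·98)/(204·203·202·201·200) = 2 × 0.0297 = 0.059. Fisher's test does not reject; Boschloo's does, because 0.059 ≤ 0.065. For 0 v 6 events, Fisher P = 0.059 × 97/199 = 0.029, and both reject.

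**True size, two-sided, 102 per arm**

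| Common event rate | Fisher | Boschloo |
|---|---|---|
| 1% | 0.04% | 0.3% |
| 2% | 0.5% | 1.6% |
| 3% | 1.2% | 2.9% |
| 5% | 2.1% | 3.6% |
| 10% | 2.9% | 3.8% |
| 20% | 3.3% | 4.5% |
| 30% | 3.6% | 4.6% |
| 35% | 3.5% | 4.8% |
| 40% | 3.8% | 4.8% |
| 50% | 4.2% | 4.2% |
| Maximum over all rates | 4.2% | 4.9% |

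If P ≤ .05 is read as one-sided, Fisher's size is 2.1% at a 5% rate, 3.5-3.7% at 20-35%, and at most 4.0%. The picture is the same.

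**Power, two-sided, 102 per arm**

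| Rates | Fisher | Boschloo | Gain (points) |
|---|---|---|---|
| 5% v 15% | 59.7% | 64.1% | 4.4 |
| 3% v 10% | 43.4% | 48.3% | 4.9 |
| 10% v 20% | 45.4% | 48.9% | 3.5 |
| 15% v 30% | 68.1% | 72.4% | 4.3 |
| 2% v 10% | 60.0% | 66.3% | 6.3 |

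Because 0.065 exceeds 0.05, Boschloo's region contains Fisher's. Its power therefore cannot be lower at any pair of rates, whatever the assumptions. For the 5% v 15%, 10% v 20% and 15% v 30% pairs, Fisher's test would need roughly 110 to 112 patients per arm to match, that is, about 8 to 10 more.

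**The case against.** The strongest reply is that nothing in section 2.8.3 is wrong. Fisher's test is standard and keeps the type I error below 5%. P ≤ .05 is a threshold, not a claim that the realised error equals 5%. Conditional versus unconditional exact testing is a choice between accepted methods. All of this stands, and it is why the point is an optional improvement.

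The reply also stands on these points:
- **No promise is broken.** No power is stated for complications or symptom relief.
- **The size figures rest on assumed rates.** Only the ordering of the two tests does not.
- **The gain is modest.** For the listed pairs, power stays between about 48% and 72% after the change, below 80% with either test.
- **Boschloo's test is not the only candidate.** The exact unconditional test based on the pooled Z statistic also has maximum size 4.9%, and reaches 67.4% for 5% v 15% and 69.9% for 2% v 10%. The containment argument, however, is specific to Boschloo's test.

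What does not stand is the step from a valid choice to nothing worth changing. The change adds no patients and no data and keeps the same error limit.

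Two stronger readings are tempting, and the documents support neither. A reader might infer that the trial's stated 80% power is undermined; it is not, because that figure comes from the Blackwelder calculation. A reader might also infer that the swap would help the primary recurrence comparison, since 2.8.3 covers all categorical indicators. It would not: the primary objective is noninferiority, with "the noninferiority margin D = 5" percent, and both procedures test for no difference. If the true rates were 30% and 35%, exactly the margin apart, Fisher's test would be non-significant 91% of the time and Boschloo's 89%. Neither result would say anything about the margin.

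**Conclusion.** A cheap improvement, not an error. At 102 per arm Fisher's test is valid but conservative. Its true two-sided size is about 1-2% at rates of 3-5%, 3-3.6% at 10-35%, lower still below 3%, and at most 4.2%. Boschloo's test recovers about 3.5 to 5 points of power for four of the listed pairs and about 6 points at 2% v 10%, with size never above 4.9%.

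The conclusion is limited to difference comparisons of binary secondary outcomes: 30-day complications and, only if it is recorded as yes/no, the symptom question. It assumes a two-sided P value, full follow-up of 102 per arm, and event rates that the documents do not give.

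**What to change.** In section 2.8.3, name a pre-specified exact unconditional test, such as Boschloo's, two-sided at 5%, for between-arm difference comparisons of binary secondary outcomes, in place of Fisher's test. Choose the test before any outcome data are seen, so that it cannot be selected on the results. State that this sentence does not govern the primary recurrence analysis.

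The cost is one sentence and possibly software other than the named SPSS package, if that package does not offer the test. No extra patients or data are needed, and nothing in section 2.5 changes.
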